#### Designing the Blog

The intervention blog was developed on the self-hosted blogging platform, WordPress [43]. We worked in collaboration with the Web designer at the Office of the Executive Vice Rector, Development, at Laval University to respect the preferences of female social media users according to our preliminary focus group study [19]. Blog features included a home page composed of a colorful header (graphic and text identifier at the top of every page) and a clear identification of the RD blogger (name, professional picture, expertise and professional credentials); an archiving system of blog posts by date and keywords to facilitate navigation; blog posts divided by subtitles and paragraphs to facilitate reading; internal and external links to references to peer-reviewed scientific papers or other reputable online resources (eg, government websites); and a comments section for interactive communication between the RD blogger and the study participants. The blog also included a Recipe page (recipes published on the blog and categorized by types of meals) and a Resource page providing supplementary healthy eating tools (eg, Health Canada Eat Well Plate [32]). Multimedia Appendix 2 provides screenshots of the intervention blog.

#### Writing Blog Posts and Creating Featured Recipes

One author (A-AD, RD blogger) wrote each post with careful attention to providing positive messages on healthy eating that were adapted to the realities of mothers of preschool and school-aged children. Posts were then reviewed by 3 authors (AL, SL, and SD) to produce a final version.

In line with the results of the preliminary focus group study [19], we included a step-by-step recipe featuring Vegetables and Fruits and/or Milk and Alternatives food groups in every post. Two authors (A-AD, AL) and their families pretested all the recipes. Recipes were described textually and with step-by-step pictures.

### Step 5: Planning Program Adoption

The aim of the fifth step of IM protocol was to plan for the adoption of the intervention. Considerations from blog adoption began as early as the needs assessment, as suggested by Bartholomew et al [17]. The specified intervention adoption outcome was that mothers in the intervention group choose to adopt the intervention as indicated by study compliance, participation, and attrition rates. In order to perform adoption outcome, mothers will have to achieve the following performance objectives: (1) complete more than 70% of study questionnaires, (2) attend over 90% of in-person appointments (compliance rate), (3) assess a minimum of 75% of the blog posts (participation rate), and (4) complete the 6-month intervention and follow-up assessment at 12 months, for a study attrition rate below 25%.

Practical applications were planned in order to stimulate mothers to use the blog. Prior to the beginning of the intervention, 2 authors (A-AD and AL) will provide instructions on how to navigate the blog website and how to post comments to all recruited mothers in order to facilitate their use of the blog throughout the study. Mothers who do not log in to the blog for 2 consecutive weeks will be reminded of the blog by email. As low actual reach, decline usage of online tools, and high attrition rates are common difficulties in Web-based interventions [44], we included engagement-promoting methods identified in previous Web-based lifestyle promotion interventions to promote mothers’ adoption of the blog and adherence to the intervention, as described below.

#### Specifying Engagement-Promoting Methods

Brouwer et al [45] found that key exposing-promoting methods that could increase the participants’ exposure to Web-based healthy lifestyle promotion interventions (eg, more average logins and longer visits on the website) were peer and counselor support, email or phone contacts and updates, and regular updates of the website. In addition, data from our preliminary study showed that women preferred RD bloggers to whom they could relate, as opposed to an unrealistic expert [19]. Recent research suggests that users of narrative health blogs identified more with the bloggers and were more likely to feel they were socially interacting with them compared with users of non-narrative blogs providing expert advice [46]. Consequently, we wrote blog posts and responses to participants’ comments in a narrative approach. By sharing personal experiences involving food, the RD blogger provided a model for mothers to aspire to.

#### Specifying Intervention Characteristics Linked to Enhanced Effectiveness

In addition to engagement-promoting methods, we developed the intervention with special attention to characteristics enhancing effectiveness in Web-based behavior change studies. Webb et al [12] showed that intervention characteristics associated with larger effect size on health-related behaviors in Web-based interventions included more extensive use of theory; incorporating multiple behavior change techniques (eg, modeling, goal setting, and provision of feedback on performance); and using additional methods of communicating with participants, such as providing access to an adviser to request advice. Kohl et al [47] found consistent evidence of effectiveness for tailored feedback, use of theory, interactivity, goal setting, and potentially social support for dietary behaviors. Accordingly, we applied multiple theory-based methods in the experimental blog, as described previously in IM Step 3. In addition to the comments function of the blog, where communication and support between the RD blogger and study participants will be promoted, the research coordinator (AL) will be available by phone or email throughout the study to support mothers with any issues related to the use of the blog website.

### Step 6: Planning for Evaluation

The aim of the sixth step of IM protocol was to plan for an effect evaluation of the intervention, which involves determining whether behavior outcomes change as a result of the intervention [17]. For this task, a randomized controlled trial will measure the effects of the developed intervention blog on dietary behaviors of mothers (Clinical Trial Protocol ID: NCT03156803).

The main objective of the study will be to evaluate the effects of the intervention blog on daily intakes of Vegetables and Fruits and daily intakes of Milk and Alternatives of mothers. As secondary objectives, we will (1) explore the effects of the intervention blog on the dietary habits of mothers’ children, including mean usual food group and nutrient intakes, (2) explore the association between mothers’ child-feeding practices and change in children dietary habits, (3) explore association between intervention blog usage and change in mothers’ dietary habits, and (4) evaluate mothers’ acceptability of the intervention blog.

#### Trial Overview

A total of 110 mothers aged 18 years old or over are being recruited in the Quebec City area of Quebec, using the following strategies: advertisement to a list of people that had indicated their interest to participate in our research institute clinical studies and to email lists of Laval University employers and students; flyers in community centers targeting families, schools, and daycares; and advertisements on Facebook. Mothers will be eligible if they have Internet access, have at least one child aged between 2 and 12 years, are primarily responsible for food purchases and preparation in the household, and consume fewer than the recommended daily serving of Vegetables and Fruits and/or of Milk and Alternatives food groups in Canada’s Food Guide (ie, less than seven servings per day of Vegetables and Fruits (560 g), and/or less than two servings per day of Milk and Alternatives). We sought participants with suboptimal dietary eating habits, and mothers were selected as the target population as they are active blog users [48] and have an important influence on the diet quality of their children [49].

**Figure 3 figure3:**
[figure not shown]
Description of the study and measurements performed at baseline, 3 months, 6 months, and 6 months after the end of the intervention blog exposure.

Eligible mothers will be randomized to the experimental group, which will include access to the blog over a 6-month period, or to a control group with a delayed exposure to the blog (Figure 3). All study participants will complete outcome assessments at baseline, 3 months, 6 months, and 6 months after the end of the intervention (T=12 months). Once baseline testing and the randomization are performed, mothers in the experimental group will receive an email including a unique identification code and a password to log in to the intervention blog and for the research team to collect log data over the intervention. In addition to login information, this email will invite mothers to consult the first published post on the blog through a Web link. Once a week for 26 weeks, mothers will receive by email an alert advertising that a new post has been published. New posts will be dated and displayed in reverse chronological order on the blog home page, making new entries easily traceable. Additionally, posts will be archived by themes, and a user “search terms” feature will be available for mothers to consult previous posts or comments throughout the 6-month intervention. These features have been identified by female social media users in our preliminary focus group study as being useful and likely to increase their use of the blog [19].

The control group will be a delayed control condition. During the 6-month intervention period, mothers in the control group will not be allowed to access the blog. They will not be contacted by the RD blogger but will meet the research coordinator (AL) at our research institute for baseline, 3-month, 6-month, and 12-month outcomes assessment. After the 12-month follow-up, mothers in the control group will be granted access to the blog’s archives containing the RD bloggers’ posts and comments to the posts’ authors by fellow study participants. Interactions with the RD blogger or study participants through the comments function of the blog will not be possible for mothers in the control group.

#### Outcome Measures

Outcome measures for effect evaluation were selected after reviewing the intervention logistic model (Figure 2) with emphasis on the evaluation of mothers’ behavior change.

##### Dietary Variables

The primary outcomes of the study are mothers’ daily servings of Vegetables and Fruits and Milk and Alternatives food groups, which will be assessed by three automated, self-administered, Web-based 24-hour dietary recalls completed by mothers at each assessment time, for two unannounced weekdays and one weekend day selected at random. Multiple administrations of 24-hour dietary recall in prospective studies that aim to determine change between points of time in mean usual intakes of groups are supported by national recommendations [50]. Recent evidence has shown that, for all food groups but the most rarely consumed, two to four dietary recalls were superior to use of Food Frequency Questionnaire data to estimate usual intake [51], and that obtaining 3 nonconsecutive days of 24-hour dietary recalls per month over a period of 6 months was adequate to estimate energy and macronutrient intakes [52]. The Web-based automated 24-hour dietary recall that will be used in this study was developed in French [53] based on the US Department of Agriculture Automated Multi-Pass Method [54] and validated among French-Canadian adults [55]. In addition to data on food groups servings [6], a list of foods and beverages selected by mothers, and macronutrients and micronutrients intakes will be obtained from The Nutrition Data System for Research (software version 4.03, Food and Nutrient Database 31) [56] and the Canadian Nutrition File (version 2015) [57] in order to assess whether changes in mothers’ daily servings of Vegetables and Fruits and Milk and Alternatives food groups will be accompanied by other dietary changes.

Mothers will complete one 24-hour dietary recall administered by an RD with the Automated Multi-Pass Method [54] for their oldest eligible child (aged between 2 and 12 years old) at each assessment time. We have chosen to administer one 24-hour dietary recall at each time point to assess children’s diet as a secondary outcome so as to not overburden mothers with questionnaires and also because the National Cancer Institute’s latest recommendations [50] support the single administration of 24-hour dietary recall to assess change in mean usual intake of a food group between two points in time. The collection of food data by a 24-hour dietary recall has been considered as an appropriate approach with children in previous studies and national nutrition surveys [5,58,59].

##### Mothers’ Child-Feeding Practices

We will assess mothers’ child-feeding perceptions, attitudes, and practices, and mothers’ relationships to children’s developing food acceptance patterns, the control of food intakes, and obesity with the Child Feeding Questionnaire [60] at each assessment time. The Child Feeding Questionnaire is a validated, self-reported 31-item questionnaire that was designed for use with parents of preschool and school-aged children [60]. Maternal child-feeding practices, such as the extent to which mothers control how much, when, and what their child eats, have been shown to impact their child’s development of food-intake controls [61].

##### Blog Usage

In line with our adoption plan of the blog (Step 5), we will explore the associations between the dose of the intervention that mothers in the intervention group received, using blog usage data, and change in their dietary habits. Over the 6-month intervention, we will monitor total number of logins, blog posts viewed, submission of comments, and the most frequently accessed links and blog pages viewed using the Web analytics service Google Analytics [62] and the Web analytics plug-in Slimstat Analytics [63].

##### Acceptability of Blog

We will explore mothers’ acceptability of the blog using focus groups at the end of the 6-month intervention blog exposure. A trained female research coordinator (AL) will use a semistructured interview guided on Patton’s recommendations [64]. A standardized open-ended interview questionnaire will be developed according to three constructs of the Technology Acceptance Model [65]: mothers’ perceptions on utility and ease of use of the blog, and mothers’ attitude (advantages/disadvantages) regarding its use to improve their dietary behaviors.

### Recruitment Procedure

We will perform a three-phase intervention study to reduce the delay between recruitment and the actual start of the intervention. We will conduct each experimental phase subsequently to allow the RD blogger to be entirely dedicated to each virtual social community. In each phase, the nutrition information and recipes in the blog will be identical, with the exception of the interaction in the comments’ section, which will be shaped by the participation in each phase. The three experimental phases will be conducted in different periods of the year (ie, winter through summer; autumn through spring; and spring through autumn), and possible seasonal variations in Vegetables and Fruits food group intakes will be tested for in our statistical model. This study was approved by the Laval University Research Ethics Committee (project n^o^2014-257 A-5 / 12-07-2016)

### Sample Size

Sample size calculations were based on a previous study investigating the effect of a dietary intervention on fiber, vegetables, fruits, and fat intake in free-living adults [66]. It was estimated that a sample size of 82 mothers would allow the detection of a 28% difference in vegetable intakes at 12 months, with a standard deviation of 2.05 in servings of vegetables, a power of 0.95 and a two-sided .05 significance level. Based on attrition rates varying between 10% and 37% in Web-based dietary behavior change interventions [67], we anticipate an attrition rate of 25% and therefore plan to recruit a total of 110 mothers.

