## Introduction

### Low Adherence to Dietary Recommendations

Lifestyle modifications—including the consumption of a balanced diet—can reduce obesity and the risk of obesity-related chronic diseases despite minimal or no weight loss [1]. Many health agencies thus recommend adopting a healthy diet to prevent obesity-related chronic diseases [2-4]. As part of a healthy diet, Vegetables and Fruits as well as Milk and Alternatives food groups are components of the Canadian adaptation of the Healthy Eating Index [5], which measures conformity to Canada’s Food Guide. Examples of Milk Alternatives included in Canada’s Food Guide are buttermilk, cheese, fortified soy beverages, kefir, paneer, pudding/custard made with milk, yogurt, and yogurt drinks [6]. Higher intakes of vegetables and fruit [5], as well as dairy product consumption [7] have been associated with improved diet quality and reduction in the risk of cardiovascular-related clinical outcomes in adults in epidemiologic studies. Despite various healthy eating public health initiatives, fewer than 50% of Canadian adults and children reach daily recommended intakes for the Vegetables and Fruits and Milk and Alternatives food groups [8]. This gap between nutrition recommendations and population dietary habits emphasizes the need to develop effective knowledge translation strategies to help individuals improve their diets.

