#### Identifying Behavioral Outcomes

Behavioral outcomes should state, in terms of behaviors, what should be accomplished as a result of the health promotion program [17]. We formulated two behavioral outcomes for the intervention based on our previous needs assessment: (1) in the next 6 months, mothers will increase their consumption of Vegetables and Fruits to include seven servings per day, and (2) in the next 6 months, mothers will increase their consumption of Milk and Alternatives to include two servings per day.

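### The 0.95 power for a 28% difference holds, on the plain reading, only if the comparison mean is about 5.9 vegetable servings a day; no such mean is stated, and it is unlikely in this population

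*Protocol article*

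**What the plan says.** The Sample Size section reads "sample size of 82 mothers would allow the detection of a 28% difference in vegetable intakes at 12 months, with a standard deviation of 2.05". The unit of that SD is vegetable servings, and the same sentence specifies "a power of 0.95 and a two-sided .05 significance level". The section takes its inputs from an earlier dietary intervention study in free-living adults, allows for 25% attrition and sets recruitment at 110. It gives no comparison mean, no difference in servings and no test. It does not say whether 2.05 is the SD of intake or of change.

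Three other places bear on how high the mean could be. Under Trial Overview, mothers qualify by eating "less than seven servings per day of Vegetables and Fruits (560 g), and/or less than two servings per day of Milk and Alternatives", and the authors say they looked for women whose eating habits were suboptimal. Under Identifying Behavioral Outcomes, the goal is that "mothers will increase their consumption of Vegetables and Fruits to include seven servings per day". The Introduction, under Low Adherence to Dietary Recommendations, reports that "fewer than 50% of Canadian adults and children reach daily recommended intakes for the Vegetables and Fruits and Milk and Alternatives food groups".

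**The concern.** A relative effect paired with an absolute SD has no fixed power until a mean is supplied. Because the paragraph prints the sample size, SD, power and significance level, the mean it relied on can be recovered. On the plain reading that mean is high for vegetables alone in a group selected largely for low intake. If the true mean is lower, 28% is a smaller number of servings, and 82 mothers give less than 0.95 power to detect it.

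The target of 82 completers rests on this one sentence. A reader who trusts it could treat a null result as stronger evidence against a 28% effect than the trial can supply.

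**Working it through.** **Inputs.** From Sample Size: 82 completers, 28%, SD 2.05 servings, power 0.95, two-sided .05, 25% attrition, 110 recruited. Assumed, because the article does not state them: equal allocation and, for the plain reading, an unadjusted two-sample t-test with 2.05 as the SD of 12-month intake.

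**The plan's own figure.** 82 / (1 − 0.25) = 109.3, which rounds up to 110. The attrition step therefore reproduces, and 82 is the total for both arms, or 41 per arm. The 82 itself cannot be reproduced without a mean, so it is solved backwards.

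**Detectable difference.** The standard error is 2.05 × √(2/41) = 0.4528.
- Normal approximation: (1.960 + 1.645) × 0.4528 = 1.63 servings.
- Noncentral t, 80 degrees of freedom: 1.65 servings.

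**Implied comparison mean.** 1.63 / 0.28 = 5.8 (normal); 1.65 / 0.28 = 5.9 (t).

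**How 5.9 fits the population.** If vegetable intake were roughly normal with mean 5.9 and SD 2.05, the share already at seven servings on vegetables alone would be P(Z > (7 − 5.9)/2.05) = P(Z > 0.54), about 30%. Once fruit averaged more than 7 − 5.9 = 1.1 servings, the mean combined intake would exceed seven and most mothers would be at or above the recommendation. That sits poorly with the Introduction's figure and with the stated search for mothers with suboptimal diets.

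**Power at lower means.** The difference is 0.28 × mean, with 41 per arm. Baseline adjustment replaces 2.05 by 2.05 × √(1 − r²), which is 1.775 at r = 0.5 and 1.464 at r = 0.7. The means and correlations are assumptions.

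| Assumed vegetable mean | 28% in servings | Unadjusted | r = 0.5 | r = 0.7 |
|---|---|---|---|---|
| 3.0 | 0.84 | 0.45 | 0.56 | 0.73 |
| 4.0 | 1.12 | 0.69 | 0.81 | 0.93 |
| 5.0 | 1.40 | 0.86 | 0.94 | 0.99 |
| Mean needed for 0.95 | – | 5.9 | 5.1 | 4.2 |

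**Other readings.** A one-sided test would need a mean of 5.3 but contradicts the stated two-sided level. Taking 82 as the number per arm would need 4.1 but contradicts the total of 110. A paired or one-sample calculation on 82 would need 2.9 but does not compare two randomized arms. Baseline adjustment is the only alternative that fits the design, and the paragraph mentions neither it nor a correlation.

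**The case against.** The strongest reply is that the documents give no expected vegetable intake for these mothers. The base, the test and the meaning of the SD may lie in the cited study or in a fuller protocol. This stands. A reader might infer that the enrolled mothers cannot average 5.9 servings, and hence that the 0.95 is shown to be overstated. The article supports neither step: 5.9 is below the cut-off of seven, and the eligibility rule is and/or, so a mother with low milk intake may enter at any vegetable and fruit intake.

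The method also matters. The outcome is measured at baseline and at three later times, so an adjusted analysis is natural, and at r = 0.7 a mean of 4.2 is enough. This stands too, and the table shows it.

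Two further inferences should be resisted. A 28% rise from 5.9 ends at 5.9 × 1.28 = 7.55, above the seven-serving goal, but that goal sets no ceiling, so this is not a contradiction. Nor can the eligibility rule be turned into a firm power figure. Take combined vegetable and fruit intake as normal with SD 2.05 and mean 5.0 to 6.5 before selection. Assume half of mothers have low milk intake, independently of the rest. Selection then lowers the SD as well as the mean, to about 1.87 to 1.92, and power for 28% of the combined intake is 0.89 to 0.97. On that scale the claim may be met or nearly met. That reading, however, sets aside the paragraph's own wording, which names vegetables twice.

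**Conclusion.** The point holds in a conditional form. On the plain reading, the printed inputs give 0.95 power for a 28% difference only at a comparison mean of about 5.9 vegetable servings a day. The article neither states nor supports that mean, and it is unlikely in a trial aimed at mothers with suboptimal diets. Most would presumably qualify on combined vegetables and fruit below seven servings, although the article does not give the split.

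The size of any shortfall is not established. At assumed means of 3.0 to 5.0, power runs from 0.45 to 0.86 unadjusted, from 0.56 to 0.94 with r = 0.5, and from 0.73 to 0.99 with r = 0.7. All of this assumes equal allocation and an SD of 2.05 servings for 12-month vegetable intake. What needs no such assumption is that the 0.95 cannot be checked as printed.

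**What to change.** Restate the detectable effect in servings. With 82 completers and SD 2.05, an unadjusted comparison has 0.95 power for a between-group difference of 1.65 servings a day and 0.80 power for 1.28.

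If 28% is kept, state the comparison mean it is taken from, whether 2.05 is the SD of intake or of change, and the test, including any baseline correlation assumed. Then print the power that follows at the baseline mean of the mothers enrolled, which the baseline recalls will supply.

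This costs one reworded paragraph and one recalculation. Recruitment stays at 110 and nothing changes in conduct. The downside is a possibly less favourable stated power.
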